## Abstract

Perinatal depression disproportionally affects underserved communities, who need effective and accessible prevention programs. Reach Out, Stay strong, Essentials for new mothers (ROSE) has demonstrated effectiveness in preventing postpartum depression in underserved populations when delivered in person. This ongoing randomized controlled trial (RCT) tests the novel virtual implementation of ROSE as universal prevention in a Federally Qualified Health Center setting. We adopted the name, La Luz, for ROSE to be culturally relevant to our population. Pregnant individuals <30 gestational weeks (target *N* = 900) are randomized to either the virtual or in-person La Luz program, which consists of four 90-min group sessions. Groups are offered in English and Spanish, based on participants’ preference. Participants complete surveys at seven timepoints: before program, 28 gestational weeks, 35 gestational weeks, and 6-weeks, 3-months, 6-months, and 12-months postpartum. Primary outcomes are postpartum depression severity measured by the 20-item Symptom Checklist (SCL-20) and 10-item Center of Epidemiologic Studies Depression Scale (CESD-10). We will perform intent-to-treat analysis to test whether virtual La Luz is non-inferior to in-person La Luz. This study also evaluates implementation process and outcomes of both modalities of La Luz to inform the development of an implementation toolkit. This RCT contributes to our knowledge of perinatal depression prevention and addresses access barriers for underserved populations. If effectiveness of virtual La Luz is demonstrated, the new evidence for a scalable low-cost prevention can be used to reduce perinatal depression and offer accessible treatment options for people who face significant barriers to care. Clinicaltrials.gov registration identifier: NCT05766475.

## Introduction

1.

Perinatal depression, the experience of elevated depressive symptoms or the occurrence of a major depressive disorder during the perinatal period (i.e., pregnancy to one year postpartum), is one of the most common complications of pregnancy [1]. It is estimated that 27.4 % of pregnant individuals globally experience elevated depressive symptoms, and 17.0 % meet diagnostic criteria for a major depressive episode, during the perinatal period [2]. Suicidal thoughts and behaviors can occur as a symptom of perinatal depression and are a leading cause of maternal morbidity and mortality [3,4]. Perinatal depression has far-reaching implications for the next generation, including premature birth, developmental delays, and vulnerability to psychopathology [5–10]. Rates of depression vary based on sociocultural factors. For example, depression is more prevalent among pregnant individuals exposed to contextual risk factors such as poverty and racism [11,12]. Systemic stressors, including systemic racism, trauma, and economic inequality, disproportionately affect those who identify as Black or African American, Hispanic/Latine, American Indian, Alaska Native, or multiple races or ethnicities, contributing to elevated rates of perinatal depression [13–15]. Further, epidemiological data indicate that Hispanic/Latine women report more persistent and severe depression [16,17]. As the population of individuals who identify as racial and ethnic minorities is growing in the United States, the health disparities experienced by minoritized pregnant individuals and their families represent an increasingly urgent public health concern.

Considering the risk for suicide and long-term adverse impact of perinatal depression, prevention efforts are critically needed [18]. Reducing perinatal depression can prevent the numerous negative outcomes it can cause for both the pregnant individual and the next generation [8,19,20]. The intergenerational benefits of addressing perinatal depression support the need for inexpensive, widely available perinatal depression prevention programs. Although several perinatal depression interventions have shown efficacy in reducing depression during pregnancy [21,22] and postpartum [23–25], it is critical to increase their reach to communities in need, particularly those at elevated risk for perinatal depression and those who experience barriers to care [11,12]. Thus, an essential next step is to ensure that evidence-based prevention programs are readily available and accessible to minoritized communities to reduce perinatal depression [26].

The Reach Out, Stay strong, Essentials for new mothers (ROSE) program [23] is a well-established interpersonal therapy-oriented group intervention for the prevention of postpartum depression [23,24]. ROSE consists of four 90-min, weekly group sessions and one individual postpartum booster session. Content addresses social support, role transition to motherhood, communication skills, and psychoeducation on postpartum depression [23,27]. Among those identified as being at risk for postpartum depression, ROSE is effective at preventing the onset of postpartum depression [23,24,27,28], with an average reduction in risk of 29 % [29], and effectiveness has been sustained through 12-month follow-up [23]. This clear and abundant evidence led the United States Preventive Services Task Force to name ROSE as one of only two established interventions effective at reducing postpartum depression [29]. Critically, ROSE has demonstrated the benefits of ROSE in preventing postpartum depression in populations that are under-served in mental health treatment, including those living in poverty as well as Black or African-American and Hispanic/Latine individuals [23,24,27,28]. Thus, there is strong evidence supporting ROSE as a postpartum depression prevention program, including among those who face health disparities. Notably, because prior trials have only tested ROSE among people who are identified as at risk for postpartum depression based on prenatal screening [23,24,27,28], implementation of ROSE as universal prevention (i.e., delivered to all pregnant people regardless of risk) remains to be tested.

Although effective perinatal depression preventions such as ROSE exist and have demonstrated promising evidence among racially, ethnically and socioeconomically marginalized populations [29], disparities in psychosocial treatment (e.g., limited access, substandard quality of care) reduce the access to effective interventions for minoritized populations [30–32]. This problem is especially apparent among Black and Hispanic/Latine individuals, who face a persistent and increasingly widening disparity in access to mental health care compared to White individuals [33,34] despite their high depression rates depression [15,35]. Although socioeconomic factors (e.g., income, insurance coverage) contribute to mental health care access, disparities remain to exist among racial and ethnic minoritized groups after accounting for these socioeconomic factors [36–38]. Additional barriers to treatment include stigma associated with mental illness, lack of culturally responsive and linguistically appropriate interventions or providers, challenges navigating the healthcare system, logistical barriers (e.g., lack of childcare), and experiences of racism and other forms of discrimination [30,36]. These barriers are particularly evident among Hispanic/Latine and Black populations [30] and contribute to a wide treatment gap among people most at-risk for perinatal depression [32,39].

The preventive intervention (i.e., ROSE) tested in this study addresses many of these barriers by adopting a universal prevention approach, delivering culturally sensitive treatment in English and Spanish, and testing telehealth delivery. Offering ROSE as a universal prevention within the obstetric setting can help improve access by normalizing and de-stigmatizing participation in prevention programs, especially for those who experience elevated social stigma and fear of negative consequences associated with being identified as needing interventions (e.g., racially and ethnically minoritized individuals) [40]. Additionally, providing services in patients’ preferred language can help reduce barriers to care and attrition by easing communication, acknowledging the patient’s language and cultural background, and facilitating bonding and sense of community among people with shared language backgrounds [30,41]. In particular, the Hispanic and Latine population is the largest, and one of the fastest-growing, racial and ethnic minoritized groups in the United States [42], and over 43 million people speak Spanish at home [43]. Additionally, the Hispanic and Latine population has one of the highest fertility rates across various racial and ethnic groups in the United States [44]. As such, providing perinatal prevention programs in Spanish when preferred can promote acceptability and adoption of these programs among Spanish-speaking pregnant individuals. However, although ROSE is available in Spanish [45], the effectiveness of ROSE in Spanish has not been empirically tested.

Expanding ROSE through virtual delivery offers another transformative strategy to improve access of care in underserved populations [46,47]. To date, trials establishing the efficacy of ROSE have only been conducted in person [23,24,27,28,48,49]. Given its widespread scalability, telehealth has the potential to enhance mental health service delivery by reducing access barriers, particularly among minoritized groups [46,47]. For example, prior research with ROSE found that Black individuals identified transportation as a major barrier [49]. Specific to perinatal depression treatment, telehealth can be an effective means of intervention [50,51]. Thus, a preventive intervention delivered via telehealth is a potentially scalable, sustainable, and effective delivery model in real-world settings.

## The current research

2.

To optimize access to efficacious preventive interventions for perinatal depression, we are conducting a randomized controlled trial (RCT) of ROSE to test the comparative effectiveness of virtual versus in-person delivery. The study design offers ROSE as a brief, low-cost treatment as universal prevention within the obstetric setting, delivers it in one’s preferred language (English or Spanish), and compares telehealth and in-person services. We adopted a name that a local non-profit, Thriving Families, uses for their ROSE program, La Luz, as this name is more culturally relevant to the population we intend to enroll. This name was chosen because “Dar a Luz” is the Spanish phrase for “to give birth”, which also has a symbolic meaning of “bring light to life.” This RCT is being implemented at Denver Health, a community safety-net hospital and Federally Qualified Health Center that serves the largest proportion of uninsured and Medicaid patients in the Denver area [52]. Patients are English- and Spanish-speaking, predominantly Hispanic/Latine and socioeconomically disadvantaged. Denver Health delivers over 4300 babies each year, which accounts for approximately a third of all babies delivered in Denver [53]. Pregnant individuals are randomized to receive La Luz either (a) in person, delivered at Denver Health, or (b) virtually, delivered by the same staff via video conferencing.

This research has two main aims. The first aim is to test the effectiveness of virtual delivery of La Luz in reducing perinatal depression compared to in-person delivery. We hypothesize that La Luz administered virtually during pregnancy will show non-inferior benefits to reducing depression as in-person delivery. The second aim is to provide recommendations for sustainability and scalability to other perinatal healthcare settings. Implementation processes and outcomes (i.e., feasibility, acceptability, appropriateness, adoption, and barriers) will be examined qualitatively and quantitatively for both the in-person and virtual interventions. Additionally, the impact of the program on patients’ healthcare service utilization will be explored and the cost of the intervention will be documented. These data will be used to develop an implementation toolkit to support sustainability, scalability, and transportability to other healthcare settings.

## Method

3.

### Participant enrollment

3.1.

#### Study population and recruitment site

3.1.1.

We aim to recruit 900 pregnant individuals from Denver Health obstetrics clinics. Pregnant individuals (18 years or older) who are English or Spanish speaking and at less than 30 gestational weeks are eligible. Individuals at 30 or more gestational weeks are excluded due to insufficient time to complete ROSE prior to delivery. The target sample size was determined based on power analyses accounting for an estimated 20 % attrition rate (10 % during pregnancy and an additional 10 % postpartum) and our primary analyses testing inferiority of virtual to in-person La Luz (see below).

Denver Health is a Federally Qualified Health Center serving low resourced and underserved pregnant individuals. The obstetrics clinics at Denver Health serve individuals from the surrounding urban metropolitan Denver area. Denver is a racially and ethnically diverse city, which is reflected in the Denver Health patient population. Among all patients who received care from Denver Health in 2023, 49 % identify as Hispanic/Latine, 13 % Black or African American, 30 % non-Hispanic White, and 4 % Asian or Pacific Islander [54]. Spanish-speaking patients make up a substantial portion of the Denver Health patient population, and some patients speak only Spanish [55].

#### Recruitment procedures

3.1.2.

Recruitment began in March 2023 and is currently ongoing. Fig. 1 provides an overview of study procedures. On-site research staff screen prenatal visits scheduled at Denver Health for inclusion criteria (<30 gestational weeks, English or Spanish speaking) using electronic health records. Patients who meet inclusion criteria are approached by the bilingual (English/Spanish) on-site project staff at their prenatal visits or via phone calls. If interested, they are scheduled for their baseline study visit. All recruitment and study procedures were approved by the Institutional Review Board at the University of Denver. The current clinical trial was registered prior to the onset of participant enrollment (clinicaltrials.gov registration identifier: NCT05766475).

### Baseline study visit and randomization

3.2.

At their baseline study visit, participants complete informed consent with research staff and the baseline survey via REDCap over the phone or via Zoom videoconferencing. At the end of their baseline visit, participants are randomly assigned to one of the two conditions (virtual or in-person) using a secure and locked computer program and are scheduled for their first group session. Research staff are blind to participants’ condition assignment during survey administration and data analysis.

### Study interventions

3.3.

#### Description of ROSE (Called La Luz in this Study)

3.3.1.

ROSE is designed as four sessions delivered prenatally with a postpartum booster session [23]. The first session covers creating realistic expectations around the postpartum period and psychoeducation on PPD, the second session addresses strategies for managing the role transition to motherhood with a focus on identifying sources of support and increasing pleasurable activities, the third session provides education on relationship dynamics and how to communicate assertively with others, and the fourth is on understanding the barriers to assertiveness and planning for the future. Throughout all four sessions, there is an emphasis on learning relaxation practices and identifying pleasant activities as coping strategies for managing changes after childbirth.

#### Virtual vs. in-person delivery

3.3.2.

We planned for the first four sessions of La Luz to be delivered prenatally in groups of 6 to 20, with a projected average of 12 per group. The group program is 90 min weekly for four weeks. The same facilitators co-facilitate the in-person and virtual modalities and across languages. Participants in both conditions are provided with workbooks by mail after their initial study intake appointment. Participants can complete any missed session by attending the session of a future cohort in the same modality or schedule an individual make-up session with the facilitator by phone or video. Following the birth of the baby, the individual booster session (typically 30–45 min) is scheduled with one of the facilitators. The booster session is delivered virtually for all participants (in both groups).

For in-person groups, transportation is provided to reduce barriers to attendance. For virtual groups, tablets with Zoom are provided to participants who need a video conferencing device. Transportation and tablets are provided to ensure that neither transportation nor technology were an inequitable barrier that negatively impacted participants’ perception or participation in the in-person or virtual groups. Participants in both conditions receive $10 for every group session they attend via a reloadable Visa card.

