#### Analysis testing inferiority of virtual vs. in-person La Luz

3.6.1.

Primary analyses will use intent-to-treat design to evaluate the effectiveness of the intervention among all enrolled participants [66]. To test whether virtual La Luz will yield a similar benefit (i.e., is non-inferior) as in-person La Luz for perinatal depression, multilevel models (timepoints nested within participants) including random intercepts and slopes will be used. Multilevel modeling accounts for nested data structure and is robust to missing data [67]. In line with non-inferiority testing, we will use a one-sided test and statistical significance set at *p* < .05 with margin of non-inferiority set to an effect size Cohen’s *d* of 0.25 for our estimate contrasts of total change in our multilevel model. Model-based total change estimate will provide us flexibility if the change over time is nonlinear (i.e., log-linear, parabolic, piecewise, etc.). A negative effect size would indicate more reduction for virtual compared to in-person, whereas, a positive effect size would indicate more reduction for in-person compared to virtual. Non-inferiority will be shown if the effect size for contrast of total change yields a one-sided 95 % upper bound smaller than *d* = +0.25. If the one-sided 95 % upper bound is bigger than *d* = +0.25, the confidence interval for the true effect size of the contrast of total change does not lie totally within the non-inferior region, and non-inferiority cannot be concluded (illustrated in Fig. 2 with ±*d* as the indicated margins). Given that intent-to-treat approaches can bias non-inferiority trials toward finding the interventions to be non-inferior, we will also conduct a sensitivity analysis including only participants who complete the intervention [68,69]. Secondary analyses will follow the same analytic procedures but with EPDS scores collected from electronic health records as the outcome.

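### The completer sensitivity analysis has no modality condition, so it does not remove remote make-up sessions from the in-person arm, and these can dilute the contrast toward non-inferiority

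*Protocol article*

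**What the plan says.** Section 3.3.2 of the protocol article gives two routes for a missed session: "Participants can complete any missed session by attending the session of a future cohort in the same modality or schedule an individual make-up session". The second route continues: "schedule an individual make-up session with the facilitator by phone or video". The same-modality limit belongs to the future-cohort route only. The individual route is not restricted to one arm, and no cap is put on the number of sessions made up this way. The same section makes the postpartum booster virtual in both arms.

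Section 3.6.1 sets the primary analysis: "Primary analyses will use intent-to-treat design to evaluate the effectiveness of the intervention among all enrolled participants". Non-inferiority is shown if the contrast of total change "yields a one-sided 95 % upper bound smaller than" d = +0.25. The section then gives a reason for a second analysis, "Given that intent-to-treat approaches can bias non-inferiority trials toward finding the interventions to be non-inferior", and the remedy: "we will also conduct a sensitivity analysis including only participants who complete the intervention". It does not say in which modality the sessions must have been received.

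**The concern.** Section 2 describes the arms as in-person delivery at the hospital and virtual delivery by video conferencing. A session made up by phone or video is not in-person delivery, so each one taken in the in-person arm moves that arm's exposure away from what its label says. If virtual delivery is truly worse, this can shrink the observed difference, and in a non-inferiority trial a shrunken difference looks like success.

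The plan sees the general risk and names a safeguard. But the safeguard removes people who dropped out and keeps people whose sessions were delivered remotely. Agreement between the two analyses could then be read as reassurance about modality when both carry the same dilution.

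**Working it through.** **Reading the two sections together.** Section 3.3.2 uses the verb *complete* for sessions made up by phone or video. Section 3.6.1 uses the same verb to define the sensitivity set and adds no condition on modality. The natural reading is that an in-person participant who made up sessions remotely is a completer. The article does not say so outright.

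**Inputs from the article.** Target N = 900 and 20% attrition (section 3.1.1); margin d = 0.25 and one-sided 5% (section 3.6.1); four prenatal sessions (section 3.3.2).

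**Assumptions.** 1:1 allocation, which is not stated; a simple two-group comparison in SD units that ignores group clustering; a true difference exactly at the margin; and a share f of the modality contrast removed by remote make-ups. The article gives no make-up rate, so f is purely illustrative.

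**Sample size.** 900 × (1 − 0.20) = 720, or 360 per arm. SE = √(2/360) = 0.0745. With a true difference of 0, power = Φ(0.25/0.0745 − 1.645) = 95.6%. No power is stated, so 900 can be neither confirmed nor refuted, and this point does not dispute it.

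**Effect of dilution.** The observed difference is 0.25 × (1 − f), so P(declare non-inferiority) = Φ(0.25 × f / SE − 1.645).

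| f | Observed difference | 360 per arm | 250 per arm (assumed completer set) |
|---|---|---|---|
| 0 | 0.250 | 5.0% | 5.0% |
| 5% | 0.2375 | 7.0% | 6.6% |
| 10% | 0.225 | 9.5% | 8.6% |
| 20% | 0.200 | 16.5% | 13.9% |

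To give f a scale: if a make-up is worth the same as a virtual session, then 20% of in-person participants each making up one of four sessions gives f = 0.20 × 1/4 = 5%. If 40% do so, f = 0.40 × 1/4 = 10%.

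**Does it always go this way?** Put the value of a make-up at r, where 0 equals a virtual group session and 1 an in-person group session. Let m_i and m_v be the shares of sessions made up in the in-person and virtual arms. The observed difference is then 0.25 × [(1 − m_i) + r × (m_i − m_v)].

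- m_i = m_v = 20%: 0.25 × 0.80 = 0.200 whatever r is, giving 16.5%.
- m_i = 30%, m_v = 10%, r = 0: 0.25 × 0.70 = 0.175, giving 26%.
- m_i = 30%, m_v = 10%, r = 1: 0.25 × 0.90 = 0.225, giving 9.5%.
- m_i = 30%, m_v = 10%, r = 1.5: 0.25 × 1.00 = 0.250, giving 5.0%, so no inflation.

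The size therefore depends on make-up rates in both arms and on how potent an individual session is. The article reports neither.

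**The case against.** The strongest reply is that the trial compares two programmes as offered, and make-ups belong to both. For that question intent-to-treat is valid and nothing has crossed over. This stands. A reader might infer that the primary analysis is biased outright; the article does not support that. The dilution concerns the narrower contrast of in-person with virtual delivery, and it arises only if the modalities differ.

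Second, completion is not defined in the article, and a full definition may sit in a document not shown. This stands in part: that remote make-ups count as completion is an inference, though the natural one. But the point is not just a missing definition. The article itself fixes the make-up rule, the purpose of the sensitivity analysis and the set it uses, and as written the first and third together defeat the second.

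Third, a make-up replaces a missed session. If it helps more than missing the session, it improves in-person outcomes relative to no make-up and makes non-inferiority harder to show. Individual sessions are also not the virtual arm's treatment, which is group video. Both are fair, and they are why direction and size cannot be settled from the article.

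Fourth, a sensitivity analysis that does not decide the verdict is normal practice. Agreed: requiring both analyses to succeed is a stricter convention, not a correction.

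The virtual booster might be read as further contamination. It is disclosed and identical in both arms, so it only means that the contrast concerns the four prenatal sessions.

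**Conclusion.** The concern holds in a limited form. In-person participants may receive any number of missed sessions by phone or video, and the one analysis offered against bias toward non-inferiority does not, as worded, take them out. If virtual delivery is truly worse, both analyses can understate the modality difference.

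The figures of 7%, 9.5% and 16.5% against a nominal 5% are illustrations at 5%, 10% and 20% dilution. They rest on 360 per arm, a true difference at the margin, proportional dilution and a make-up rate that the article does not give. The inflation could be smaller or nil. The article does not support a statement that the trial's result will be biased, or by how much.

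**What to change.** Section 3.1.2 describes recruitment as ongoing, so the following can still be settled before analysis:

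1. Record the mode of every session in both arms: group session in the assigned modality, or individual by phone or video. The $10 payment described in section 3.3.2 is for group sessions attended, so it cannot be relied on to show how a make-up was delivered.
2. Keep the completer analysis and add a set defined by a pre-stated minimum number of the four prenatal sessions received as group sessions in the assigned modality. Apply the same criterion to both arms, so that make-ups are not penalised in one arm only.
3. Report the share of sessions made up remotely, by arm.
4. State in advance that a discordant result in this set will be reported as limiting the non-inferiority conclusion.

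The cost is one data field, some plan wording and a smaller, less precise set. By the power formula above, an assumed 250 per arm gives Φ(0.25/√(2/250) − 1.645) = 87.5%, against 95.6% with 360. The set is still selected after randomisation, so it informs the intent-to-treat result and does not replace it. Weighting for the probability of adherence, or requiring both analyses to meet the margin, are optional. The make-up rule itself need not change.
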